**FIGURE 4 F4:**
[figure not shown]
The HPLC chromatograms of astragaloside A and NTF capsules. **(A)** The control sample (astragaloside A) solution-10 μL; **(B)** The control sample (astragaloside A) solution-30 μL; **(C)** The test sample (NTF capsules) solution-20 μL.

Preparation of control sample solution: An appropriate amount of the control sample-astragaloside A was accurately weighed, and methanol was added to prepare a solution containing 0.06 mg per 1.0 mL. Preparation of test sample solution: Approximately 1.0 g of the test sample-NTF capsules was weighed, mixed in 20 mL of water, shaken, and extracted 4 times using n-butanol mixed with the saturating water, 20 mL each time. The extracts from the 4 rounds were combined, washed twice with the ammonia test solution, 10 mL each time, and then washed twice with the water saturated mixture of n-butanol, 10 mL each time. It was then evaporated to dryness with n-butanol solution, the residue was dissolved in methanol, and transferred to a 5 mL-volumetric flask. Finally, methanol was added to the scale, shaken, and filtered to collect the filtrate.

Ferulic acid (C_10_H_10_O_4_), i.e., the main active ingredient of Conioselinum anthriscoides “Chuanxiong” [Apiaceae] in NTF capsules was 0.21 mg/g. The specific analysis method was as follows: CAPCELL PAK C18 TYPE MG (4.6 × 250 mm, 5 μm), column temperature 30°C; Methanol – 2% acetic acid solution (18:82) was used as mobile phase at a flow rate of 1.0 mL/min. The ultraviolet detector was used to record at a wavelength of 323 nm. 10 μL of the control product (ferulic acid) solution and 10 μL of test product (NTF capsules) were injected into the HPLC for measurement, respectively. The chemstation software was used to collect and calculate data based on the external standard method (Figure 5).

**FIGURE 5 F5:**
[figure not shown]
The HPLC chromatograms of Ferulic acid and NTF capsules. **(A)** The control sample (Ferulic acid) solution-10 μL; **(B)** The test sample (NTF capsules) solution-10 μL.

Preparation of control sample solution: An appropriate amount of control sample-ferulic acid was weighed and placed in a brown measuring flask. A concentration of 45% ethanol glacial acetic acid (20:1) solution was added to prepare a solution containing 10 μg per 1.0 mL. Preparation of test sample solution: Exactly 1.0 g of the test sample - NTF capsules content was weighed and placed in a conical flask with a stopper. We then added 40 mL of 45% ethanol glacial acetic acid (20:1) solution into the flask, sealed it tightly, heated, and refluxed for 1.0 h after weighing. It was then cooled and weighed again. Next, 45% ethanol glacial acetic acid (20:1) solution was added to make up for the lost weight, vigorously shaken, and centrifuged. The supernatant was filtered to obtain a clean sample.

Hinye Pharmaceutical Co., Ltd. manufactured NTF capsules and placebo. According to the Chinese Pharmacopoeia (2015) (Chinese Pharmacopoeia Commission, 2015), the entire production process of IP strictly adheres to good manufacturing practice (GMP) standards. Besides, the production process conforms to the quality specification standards. The quality-checked IP will be delivered to each clinical research sub-center. The medication administrator in every research sub-center receives and manages drugs following good clinical practice (GCP) requirements. Storage conditions: room temperature within 25 ± 2°C and relative humidity range of 60 ± 10%.

### Group assignment and intervention

Participants will be stratified and denoted by Y or N according to the presence or absence of clinical manifestations of brain damage (cognitive decline, mood disorders, swallowing disorders, unstable gait, prolonged dizziness). Y and N groups will be divided into intervention groups (denoted by Y-T and N-T) and control groups (denoted by Y-C and N-C) using the stratified block randomized method with SAS statistical software.

Different doses of NTF capsules will be given to the Y-T and N-T groups, i.e., the Y-T group will be administered 4 capsules thrice daily with warm water, half an hour after breakfast, lunch, and dinner. In contrast, the N-T group will be given 4 capsules twice daily with warm water, half an hour after breakfast and dinner. The Y-C and N-C groups will receive the placebo. The dose and usage of the placebo in the Y-C and N-C groups will be similar to that in the intervention groups. The treatment for the four groups will last 6 months.

In each center, every participant will be assigned a clinical research coordinator (CRC) responsible for allocating drugs based on whether they have clinical manifestations of brain damage and recruitment sequence before filling out the dispensing record form.

### Randomization

This study uses a stratified block randomization approach. The participants were grouped into HT-CSVD with clinical manifestations of brain damage and HT-CSVD without clinical manifestation of brain damage based on the presence or absence of clinical manifestations of brain damage. An appropriate block length was selected (the size of block is 4) and random assignment was conducted using the SAS 9.4 statistical software (SAS Institute, North Carolina, United States) developed by statisticians from the Drug Clinical Evaluation Research Center of Central South University. 194 random sequences were generated for each group, that is, the randomized coding table with No. 001-194 was developed. The participants of each group were randomly divided into the intervention group and the control/placebo group at an allocation ratio of 1:1. Randomized codes were used as the drug numbers which were kept in an opaque sealed envelope and taken to Hinye Pharmaceutical Co., Ltd. (Changsha Hunan, China) for unified drug label production. The identification code of each subject was similar to the drug number.

### Blinding

The trial is a double-blinded design in which all the investigators, clinical observers, and participants are blinded to treatment assignments. Randomized codes will be completed by the statisticans. The allocation of unique codes for each group will be managed by the staff of Hinye Pharmaceutical Co., Ltd.

The record of the blinding process will be kept as one of the clinical trial documents. The contents of the blinding record include drug preparation, drug packaging, usage, storage and assignment, generation of randomized codes, drug box production, emergency letter, test report of NTF capsules and placebo, the storage of blinding codes, rules for breaking blind law and dispensing numbers of each research center.

Blinded coding, initial randomization number, block length, and other parameters are sealed into two copies. For proper storage, the two copies were handed to the leader of the five clinical research sub-centers and trial sponsor of the study at the Department of Drug Clinical Trial Administration in the First Hospital of Hunan University of Chinese Medicine, and Hunan University of Chinese Medicine, respectively. The blinding codes will be kept strictly confidential by an impartial third party and remain sealed until statistical analysis at the end of the trial. The assignment codes will be opened only in case of a AEs relevant to the IP and other emergencies.

### Data collection

#### Baseline data

Baseline data, including general demographic information, past medical history, symptoms and signs, history and treatment of HT, brain MRI, TCM syndrome scores, cognitive and depression scales and safety evaluations will be collected. The content includes the subject’s Age, gender, occupation, body mass index (BMI) and clinical BP, main symptoms and signs, history of basic diseases and medication, TCM syndrome scores, mini-mental state examination (MMSE) and Hamilton depression (HAMD)-17 scores, brain MRI (Fazekas scores, dVRS grades, number of LI and CMB), electrocardiograph (ECG) and laboratory parameters including blood routine, urine and stool routine, liver and kidney function, blood lipids, fasting plasma glucose (FPG), glycosylated hemoglobin A1c (HbA1c), myocardial enzyme spectrum and coagulation routine.

#### Assessment data

After 3 and 6 months of treatment, the subjects’ clinical BP, main symptoms and signs, disease history and medication use, TCM syndrome scores, MMSE and HAMD-17 scores will be assessed. Laboratory examination results will be collected respectively, such as blood routine, urine and stool routine, liver and kidney function, blood lipids, FPG, HbA1c, myocardial enzyme spectrum and coagulation routine, and ECG. The onset time, cause, and treatment of AEs will be recorded in the case report form (CRF), including an analysis of whether AEs are associated with the IP, completion and suspension time of the trial. Brain MRI will be assessed after 6 months of treatment (included Fazekas scores, dVRS grades, number of LI and CMB).

### Indicators detection

The clinical BP will be measured at 8–9 am in a fasting state using an upper arm electronic sphygmomanometer, such as TM-2655P, TM-2656VP (A&D Company, Ltd., Tokyo, Japan) or HEM-7124(Omron Company, Ltd., Dalian, China). The subjects should rest for 10–15 min before BP measurement, then take a sitting position with the palm stretched upwards, the elbow at the heart level, the upper arm at 45° to the torso, and the hand relaxed without clenching the fist. The patient should wait for a while if any abnormality is found during the BP measurement. The interval between two measurements should not be less than 5 min, the site and position of the measurement should be similar. Brain MRI will be performed using the US GE SignaHDxt 3.0T or 1.5T.

During the run-in period and the treatment periods, 3–5 ml of peripheral venous blood will be drawn from all subjects in the morning on an empty stomach, then left to stand for 1–2 h. Whole blood, serum, and plasma supernatant (extracted after centrifugation at 3,000 rpm for 10–15 min) will be taken for laboratory biochemical examination, including blood routine, myocardial enzyme spectrum, liver and kidney function, blood lipids, FPG, and HbA1c. Meanwhile, three tubes of midstream specimen of urine from each subject will be taken for urine sediment microscopy, urine routine, and microalbumin analysis. Appropriate stool samples will be kept for stool routine and occult blood tests. Laboratory biochemical examination will be performed using the cobas8000 (702/502), cobas U601/701 Roche automatic biochemical analyzer, and SYSMEX-Xi9000 hematology analyzer.

### Types of outcomes

#### Primary outcome

The Fazekas scores and dVRS grades will be obtained for both groups. The specific scoring criteria are described in the diagnostic criteria. Brain MRI examinations will be performed before enrollment and after 6 months of treatment.

#### Secondary outcomes

The number of LI and CMB will be examined using brain MRI before enrollment and after 6 months of treatment (specific scoring criteria are described in diagnostic criteria). Clinical BP, FPG, HbA1c, blood lipids (TC, HDL-C, LDL C, TG, ApoA1, ApoB), coagulation routine (PT, APTT, FIB, TT), TCM syndrome scores, and MMSE scores will be collected before enrollment and after 3 and 6 months of treatment, respectively. TCM syndrome scores will be obtained for cardinal symptoms of hard breath or fatigue, pain, amnesia, hemiplegia, limb numbness and dizziness (None = 0, Mild = 2, Moderate = 4, Severe = 6), and minor symptoms of spontaneous sweating, lazy speech, phlegm and mania (None = 0, Mild = 1, Moderate = 2, Severe = 3), with total scores of 0–48 (Zhen, 2002). The maximum scores are 30 in MMSE scale. Scores of 27–30 are considered normal, whereas scores <27 are considered a cognitive impairment. Dementia severity grading: The total scores of MMSE scale≥ 21 for mild, 10–20 for moderate, and ≤9 for severe (Folstein et al., 1975).

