**Conclusion:** The protocol will comfirm whether naotaifang capsules reduce Fazekas scores, dilated Virchow-robin spaces grades, and the number of lacunar infarctions and cerebral microbleeds, clinical blood pressure, increase mini-mental state examination scores, traditional Chinese medicine syndrome scores of Qi deficiency and blood stasis (QDBS), and improve the quality of life of subjects. The consolidated evidence from this study will shed light on the benefits of Chinese herbs for hypertensive cerebral small vessel disease, such as nourishing qi, promoting blood circulation and removing blood stasis, and dredging collaterals. However, additional clinical trials with large samples and long intervention periods will be required for in-depth research.

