#### Diagnostic criteria of cerebral small vascular disease

According to the “Chinese Consensus on Diagnosis and Therapy of CSVD” (Huang, 2015) and Standards for ReportIng Vascular changes on nEuroimaging (STRIVE v1) (Wardlaw et al., 2013), CSVD is primarily characterized by stroke (small deep infarction and cerebral hemorrhage), cognitive and emotional impairment and overall functional decline. Based on brain MRI, prominent manifestations include lacunar infarction (LI), WMH, dVRS, CMB, and cerebral atrophy (Figure 3). The imaging features include:(1) Number of LI: (a) Old LI: round or oval, with a maximum diameter not exceeding 15mm, distributed under the cortex, T1 and T2 are cerebrospinal fluid signals and T2 fluid-attenuated inversion recovery (FLAIR) is a ring of low signal in the center and high signal around it; (b) Acute LI: round or oval, with a maximum diameter not exceeding 15 mm, subcortical distribution, high signal on diffusion-weighted imaging (DWI) and negative on conventional MRI.(2) WMH of vascular origin: It shows abnormal signals, and different ranges and sizes in the white matter. Such as an equal signal or low signal in T1, a high signal in T2, or T2 FLAIR without a cavity. The severity of cerebral white matter lesion (WML) is based on the Fazekas scores (Fazekas et al., 1987); for instance, changes in paraventricular hyperintensity, such as no lesions, cap-like or pencil-thin lesions, smooth halo, irregular paraventricular hyperintensity, extend to the deep white matter, rated as 0, 1, 2, and 3 points respectively; the signal changes in the deep white matter, such as no lesions, spot-like or small-piece lesions, extensive patchy lesions beginning to fuse and large-area fusion of lesions, score 0, 1, 2 and 3 respectively. The total scores are 0–6 points. WMH caused by other non vascular diseases should be excluded, such as multiple sclerosis, white matter dystrophy, etc.(3) dVRS grades (Doubal et al., 2010): The gap that passes through the gray or white matter and is consistent with the course of blood vessels. Round or oval or linear, with smooth margins, maximum diameter exceeds 3 mm, located in the distribution area of perforating arteries, all sequences are consistent with cerebrospinal fluid signal, T2 FLAIR has no surrounding hyperintensity ring (except when it crosses the WMH area), DWI has no diffusion restriction. (a) In the basal ganglia, the level with the most dVRSs prevails, and the severity is rated as 4. The classification is as follows: Grade 0 = no dVRS, Grade 1 ≤ 5 dVRS, Grade 2 = 5–10 dVRS, Grade 3 ≥ 10 dVRS, but the number of dVRS is still countable. The number of dVRS Grade 4 is difficult to count, and Grade 4 has cribriform changes in the basal ganglia. (b) In the white matter area, dVRS severity scoring criteria: Grade 0 = no dVRS, Grade 1 ≤ 10 dVRS, Grade 2 ≥ 10 dVRS (but the largest level of dVRS is < 10), Grade 3 = 10–20 dVRS at the maximum number level and Grade 4 ≥ 20 dVRS at the maximum number level.(4) CMB: Round or oval, well-defined, homogeneous susceptibility-weighted imaging (SWI) signal focal [computed tomography (CT) is not shown in T1, T2, T2 FLAIR], the diameter is 2–10 mm, and the lesion is surrounded by brain parenchyma. A hypointense signal <2 mm seen on 1.5T MR may only be the missing signal in one voxel, and the artifact cannot be ruled out.(5) Cerebral atrophy: Reduction of brain volume unrelated to specific focal injury.

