### Statistical analysis

All statistical analyses will be performed using the SPSS 22.0 statistical software. Descriptive statistics will be used for baseline characteristics data. Quantitative variables (numerical variables) will be analyzed by the normality test (such as *Shapiro-Wilk*), and normal distribution numerical variables will be compared using two independent *t*-tests or analysis of variance (*ANOVA*) and other potential confounding variables (such as multicenter characteristics) as covariates. Numerical variables will be summarized with mean ± SD. Non-parametric tests (*Wilcoxon rank-sum* test, *Kruskal–Wallis* test) and M (P_25_, P_75_) will be used to describe the non-normal distribution. Qualitative variables (categorical variables) are represented by the number of cases and the composition ratio; comparison among groups will be performed using the chi-square test or Fish precision probability. Non-parametric test or analysis of covariance will be used to compare the difference in therapeutic indexes. The efficacy analysis adopts the intention to treat (ITT) analysis and the per-protocol set (PPS). Subgroup analysis will be performed regardless of whether the treatment significant effect the main outcome. Safety analysis will be performed by analyzing the incidence of intergroup AEs and abnormal laboratory examination results before and after treatment.

The full analysis set (FAS) will be conducted for the therapeutic indexes of all subjects included in the study. Statistical analysis in accordance with PPS will be conducted for the therapeutic indexes of subjects completing the drug intervention for 6 months. FAS uses the last-observed-carried-forward method (LOCF) to adjust the missing data and complete ITT analysis. The safety analysis will be performed using the safety analysis set (SS). All statistical tests will be two-sided. *p* ≤ 0.1 means there is a statistical difference, *p* ≤ 0.05 represents a significant statistical difference.

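### LI and CMB are defined as lesion totals, with old and acute LI pooled: a fall is not evidence of benefit, and power depends on a baseline adjustment that the plan does not fix

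*Protocol article*

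**What the plan says.** The Secondary outcomes section of the protocol article states: "The number of LI and CMB will be examined using brain MRI before enrollment and after 6 months of treatment". It refers to the diagnostic criteria for how lesions are scored. Table 1 and the Assessment data section also name the number of lesions. No section defines a new lesion.

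The diagnostic criteria for cerebral small vessel disease put two kinds of lesion under the single item for the number of LI:
- an old LI, for which "T1 and T2 are cerebrospinal fluid signals";
- an acute LI, recognized by "high signal on diffusion-weighted imaging (DWI) and negative on conventional MRI".

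The abstract's conclusion says the trial will show whether the capsules "reduce Fazekas scores, dilated Virchow-robin spaces grades, and the number of lacunar infarctions and cerebral microbleeds". The Introduction instead speaks of preventing progression. The sample size section assumes that the treated mean Fazekas score stays at 2.29 while the control mean rises to 2.8.

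On analysis, the Statistical analysis section says: "Non-parametric test or analysis of covariance will be used to compare the difference in therapeutic indexes". For normally distributed variables it mentions "other potential confounding variables (such as multicenter characteristics) as covariates". It does not name the baseline value as a covariate, and it does not say whether the difference is a change from baseline. The threshold for a statistical difference is 0.10, two-sided.

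**The concern.** A treatment that prevents progression acts on lesions that appear after baseline. The total on the month-6 scan also contains every lesion already there, and patients differ far more in that burden than in what six months can add.

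For LI there is a second problem. An acute LI counts only through its DWI appearance. If it loses that appearance and does not become a lesion with cerebrospinal fluid signal, it meets neither definition and leaves the count without any treatment. The net change in LI is then new lesions minus lesions that dropped out, and a fall can occur on placebo.

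Two things are at stake: how a reported reduction is read, and the power of the arm comparison for these two outcomes.

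**Working it through.** **The plan's own figure.** The sample size rests on Fazekas scores only; nothing is stated for LI or CMB. The formula gives (1.65 + 0.85)² × (1.26² + 1.3²) / 0.5² = 6.25 × 3.2776 / 0.25 = 81.94, against a stated 81. Then 81 × 1.2 = 97.2, and 97 × 4 = 388. The total reproduces. It supplies only the arm size used below: 388 / 2 = 194, and 194 × 0.8 ≈ 155 per arm.

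**Structure of the count.** Let B be the baseline count, N the new lesions, and F the baseline acute LI that no longer meet either definition at month 6. Then:
- month-6 total = B − F + N;
- net change = N − F;
- new lesions = N.

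For CMB, F = 0 under these definitions, so net change equals new lesions.

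**One setting by hand, at 0.10.** Assume a baseline mean of 2, new lesions 0.3 on control and 0.15 on treatment, F = 0, and a patient-level gamma factor of shape 1 shared by B and N, so that a count with mean m has variance m + m².
- Totals: means 2.3 and 2.15, variances 7.59 and 6.7725. The standard error is √(14.3625/155) = 0.304, so z = 0.15/0.304 = 0.49 and power is about 14%.
- New lesions: variances 0.39 and 0.1725. The standard error is √(0.5625/155) = 0.060, so z = 0.15/0.060 = 2.49 and power is about 80%.
- Share of the control month-6 variance explained by baseline: 6.6² / (6 × 7.59) = 0.96.

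**Simulation A, smaller effects.** 155 per arm, two-sided 0.10, 1000 runs per setting. All lesion rates are assumptions: baseline mean 2 or 4, 0.1 or 0.3 new lesions per control patient, halved by the drug. Power, with rank-sum tests except for ANCOVA:

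| Baseline lesions acute; share of those lost | Month-6 total | Net change | ANCOVA with baseline | New lesions |
|---|---|---|---|---|
| none | 10–15% | 45–77% | 47–86% | 45–77% |
| 5%; 50% | 9–14% | 27–71% | 27–78% | 45–78% |
| 10%; 70% | 10–13% | 19–67% | 20–70% | 44–77% |

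The baseline count explained 93–99.5% of the variance of the control month-6 total. Where acute LI could drop out, 3–19% of control patients showed a fall, and the control mean change ran from +0.25 to −0.18. With no drug effect (baseline mean 3, 0.2 new lesions in both arms, 10% acute, 70% lost), the rejection rate was 0.08–0.12 against a nominal 0.10.

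**Simulation B, larger effects.** 155 per arm, two-sided 0.05. Assumed: negative binomial baseline count with mean 1 to 4, new lesions 0.3 vs 0.1 or 0.4 vs 0.15, 5–30% of patients with one acute LI, half of which leave no cavity.

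| Analysis | Power |
|---|---|
| Month-6 total | about 6–26% |
| Rank-sum on net change | 61–84% |
| ANCOVA with baseline count | 78–90% |
| New lesions | 85–89% |

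A rerun at the plan's 0.10, with baseline means 1 and 4 and overdispersed new lesions, gave 86–96% for ANCOVA and 92–94% for new lesions.

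**The case against.** Several points on the other side stand.

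- A reader might infer that the plan compares raw month-6 totals. The text does not say so. It speaks of a difference and permits ANCOVA, which fits a change score or a baseline-adjusted analysis at least as well. What remains is that it commits to none of these.
- A reader might also infer that fading acute LI could create a false treatment effect. They are expected to fade equally in both randomized arms, and the simulated false-positive rate stayed near nominal. Only a within-arm reading misleads.
- That a real effect is likely to be missed does not follow in general. Baseline-adjusted ANCOVA came close to new-lesion counts on the larger-effect inputs, and closer still at 0.10.
- Fading concerns LI only. No section states that old lesions persist or that acute LI disappear; both are inferred from the imaging definitions, and the frequencies are assumed. The four-week run-in and the exclusion of unstable underlying disease suggest few acute LI. They are not excluded, though: an LI of either kind can establish the diagnosis.
- The aim of reducing the number comes from one sentence of the abstract, and the sample size section shows that the working hypothesis is less progression than placebo. This argues for aligning the wording, not against the point.
- A condensed article may leave the test and the reading procedure to a fuller document. The outcome variable, the pooled LI definition and the direction of the aim are, however, stated here.

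**Conclusion.** The point holds as a matter of outcome definition and interpretation, with moderate weight because these are secondary outcomes in a trial that calls itself exploratory. The month-6 number is mostly baseline burden. For LI, the net change mixes new lesions with acute lesions that no longer qualify, so a fall within an arm is not evidence of benefit. The between-arm test is not biased by this, but it can lose power.

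The size of the loss depends on an analysis the plan leaves open. In simulation B it is large only for raw totals. In simulation A, with rarer events and heavier fading, net change and ANCOVA also fall short of new-lesion counts for LI (20% against 44% at worst for ANCOVA). With no fading, as for CMB, they lose nothing. All of these figures rest on assumed lesion rates and overdispersion.

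**What to change.** Before unblinding (if the codes are already open, label the change post hoc):

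1. Define the two outcomes as the number of new LI and the number of new CMB at month 6 that were absent on the baseline scan. A baseline acute LI that has become a lesion with cerebrospinal fluid signal is not new; one that no longer meets the definition is not a reduction.
2. Tabulate acute and old LI separately at both scans.
3. Compare arms with a count model, such as negative binomial, that includes the baseline count and the Y/N stratum. The simulations tested new lesions by rank-sum, so the power of this model was not itself computed.
4. Reword the aim as fewer new LI and CMB than on placebo.

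If only totals were recorded and re-reading is not feasible, at least fix the analysis as the month-6 count adjusted for the baseline count. Where the two types were recorded separately, exclude acute LI from the LI count or show them apart.

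Cost: no new scans or visits. Table 1 gives recruitment as completed, so the work is blinded paired reading of existing images by the existing readers, for up to 388 patients if only totals were kept.
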